### Data analyses

#### Diagnostic study

All items of the examination protocol will be compared between CTA positive and CTA negative patients. In order to show the importance of any single variable in the decision making process the variables will be compared both within all included patients and in subgroups. Using the Classification and Regression Trees (CART) method [37] the decision making process will subsequently be reconstructed into a decision tree for predicting continuous dependent variables (regression) and categorical predictor variables (classification). The decision tree will be compared to the reconstructed decision process from the Christensen study comprising chronic chest pain patients [26]. The agreement between the old and the new decision tree will be analyzed. Further, the proportion of CTA positive patients within the group of patients with normal MPS will be compared to proportion in the group of patients with abnormal MPS.

#### Randomized controlled trial

The size of the study sample was estimated using data from the study by Christensen et al. [27]. In this study, patients with suspected chronic stable angina pectoris were included. Improvement in chest pain over the last two weeks was assessed using an ordinal 5-point box scale. Using these results, a sample of 120 patients will provide 81% power to detect a shift in the distribution of the improvement in chest pain from 0%/5%/25%/45%/25% to 1%/10%/40%/40%/9%, which corresponds to the findings in the study by Christensen et al. The two studies are not similar in terms of patient characteristics (chronic versus acute chest pain), rating scales (5-point box scale versus 7-point box scale) or assessment period (two weeks versus one week). Nevertheless, a sample size of 120 patients was deemed sufficient.

The baseline scores of the patient demographics (e.g. age, gender, duration and history of complaints), primary and secondary outcomes will be used to compare the two intervention groups. Differences between baseline and follow up measurements will be calculated and compared. If necessary, adjustment for baseline variable will be made, using analysis of covariance (ANCOVA). A confirmatory, secondary analysis using the repeated measures, multivariate analysis of covariance (MANCOVA) will be used as an overall test for differences between groups. This will include both the primary and secondary patient-rated outcomes. The statistical analysis will be performed on the basis of the intention-to-treat principle, i.e. patients will be analysed in the treatment group to which they were randomly allocated. Finally, based on a prior definition of success, numbers needed to treat will be calculated. Outcomes of patient rated improvement will be dichotomized and success will be defined as patients rating "better" or "much better".

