#### Primary outcome measures in the RCT

Participants are asked to rate their worst level of chest pain during the last week, using an ordinal 11-point box scale (0 = no pain, 10 = the worst pain possible). Improvement in chest pain is rated by participants on a 7-point ordinal scale with responses ranging from "much worse" to "much better".

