### Outcome measures

We have chosen global perceived effect as one out of two primary outcome measures even though critique has been posted on the reliability and validity of global rating scales [39]. Global rating scales are typically correlated with the patients' present status and are not an unbiased measure of change. However, global rating scales are regarded as clinically relevant and valid, and responsive to measure patients' perceived recovery. The global rating scale was also chosen, because during the pilot study we found that pain intensity levels were relatively low compared to for instance patients seeking care for low back pain. Patients initially reported very high levels of pain which then spontaneous decline in intensity within a very short period of time (hours to days), rendering pain a less than optimal primary outcome measure. Finally, we found that the Patient Specific Functional Scale [33] would not make a good primary outcome measure because many patients experience a first time episode of chest pain and, thus, do not feel limited in their daily activities.

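### The stated RCT analysis (change from baseline, ANCOVA only conditionally) cannot be formed for the improvement primary and is generally not the most precise choice for worst pain

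*Protocol article*

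**What the plan says.** The article's section on primary outcome measures in the RCT names two primaries. The first is pain intensity: "Participants are asked to rate their worst level of chest pain during the last week, using an ordinal 11-point box scale". The second is a global rating: "Improvement in chest pain is rated by participants on a 7-point ordinal scale", running from much worse to much better. The Discussion, under Outcome measures, confirms the status of the second: "We have chosen global perceived effect as one out of two primary outcome measures".

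The data-analysis section for the randomised trial bases the sample size of 120 on a shift in the distribution of improvement and states 81% power. It then describes the analysis in general terms for all outcomes. Baseline values of demographics and of the "primary and secondary outcomes will be used to compare the two intervention groups". Next, "Differences between baseline and follow up measurements will be calculated and compared". Then comes the conditional step: "If necessary, adjustment for baseline variable will be made, using analysis of covariance (ANCOVA". The article gives no criterion for that condition and does not name the baseline variable.

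The only step specific to improvement comes at the end of the section: the rating is dichotomised so that a number needed to treat can be calculated.

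**The concern.** Two things look wrong, one for each primary.

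- **Improvement.** A transition rating is itself a report of change. Nothing is rated at baseline, so there is no baseline score to compare between groups, no difference to calculate, and no own-baseline covariate for ANCOVA. The outcome on which the trial was sized is therefore left without a workable between-group test in the method the article sets out, and the analysis described is not the one that was powered.
- **Worst pain.** A baseline value exists, so the method can be carried out. But the default is the unadjusted change score, which generally has a larger variance than ANCOVA. ANCOVA enters only under a condition nobody has defined. That costs precision and leaves the analyst a choice of model once the data are visible.

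**Working it through.** **1. The plan's own figure.**

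Inputs from the sample-size paragraph: 120 patients, and improvement distributions 0/5/25/45/25% and 1/10/40/40/9%. The Randomization section gives 1:1 allocation, hence 60 per arm. Assumed, because the article does not state them: two-sided 5% and no dropout.

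- Probability that a patient from the first distribution rates higher than one from the second, counting ties as half: 0×0.005 + 0.05×0.06 + 0.25×0.31 + 0.45×0.71 + 0.25×0.955 = 0.63875. The distance from 0.5 is 0.13875.
- Null standard error with tie correction. The averaged category proportions are 0.005, 0.075, 0.325, 0.425 and 0.17, and their cubes sum to 0.1164. The variance is (1 − 0.1164)/12 × 120/(60×60) = 0.002454, so the standard error is 0.0495.
- Standard error under the alternative: √[(0.0711 + 0.0610)/60] = 0.0469.
- Power = Φ[(0.13875 − 1.96×0.0495)/0.0469] = Φ(0.888) = 81.3%.

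A simulation of 20,000 trials with the continuity-corrected test gave 81.5%. The stated 81% is therefore reproduced by an ordinal Wilcoxon comparison of the ratings themselves. Nearby methods give 82.4% (proportional odds) and 82.7% (t-test on the category scores). None of these is a comparison of baseline-to-follow-up differences.

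**2. Can the described analysis be applied to improvement?**

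| Step in the article | Worst pain | Improvement rating |
|---|---|---|
| Baseline score compared between groups | exists | does not exist |
| Difference from baseline to follow-up | exists | cannot be formed |
| ANCOVA on the outcome's own baseline | possible | not possible |
| Dichotomy for number needed to treat | not planned | planned, no test named |

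**3. Precision for worst pain.**

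Let r be the correlation between baseline and follow-up pain, and k the baseline SD divided by the follow-up SD. The article gives neither. In units of the follow-up variance, in large samples:

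- change score: 1 + k² − 2rk
- ANCOVA on baseline: 1 − r²
- ratio: (1 + k² − 2rk)/(1 − r²)

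With equal SDs (k = 1) the ratio reduces to 2(1 − r)/(1 − r²) = 2/(1 + r):

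- r = 0.2: 2/1.2 = 1.67
- r = 0.5: 2/1.5 = 1.33
- r = 0.8: 2/1.8 = 1.11

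With unequal SDs at r = 0.5:

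- k = 0.5: (1 + 0.25 − 0.5)/0.75 = 1.00
- k = 1.5: (1 + 2.25 − 1.5)/0.75 = 2.33

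The ratio can also be written 1 + (k − r)²/(1 − r²). It is never below 1 and equals 1 only when k = r. So the direction is settled, but the size for this trial is not.

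**The case against.** The strongest reply is that this is a condensed article. The sentence on differences is generic and does not name improvement, and sizing the trial on a distributional shift already points to an ordinal comparison. Naming the test could be left to an analysis plan that is not shown. Part of this stands: silence about a test would be no finding, and ANCOVA of improvement on some other baseline variable, such as baseline pain, would be feasible. What remains is that the article does set out a method for the outcomes in general, and that method does not fit one of its two primaries.

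On pain, it is fair to reply that randomisation makes the change score unbiased, so validity is not at issue. That stands.

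Several stronger readings are tempting but not supported:

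- **That a significance test of baseline balance triggers ANCOVA.** The article does not say so; only the order of the sentences suggests it. Even a fixed rule of that kind did not inflate type I error in simulation (3.9% to 4.5% for r from 0.2 to 0.7). Reporting whichever of the two analyses is more favourable gave 6.5% to 7.9%, but the article does not propose that. The fault is that the condition is open.
- **That pain power falls to about 59–69%.** This assumes r between 0.2 and 0.5, equal SDs, and 81% power for pain. The 81% belongs to improvement. Equal SDs are doubtful when the Discussion describes very high initial pain that declines rapidly.
- **That improvement will have about 65% power.** This takes the top two of five planning categories (70% against 49%) as equivalent to the two success categories of the seven-point scale. The article does not label the five-point scale and uses the dichotomy only for the number needed to treat.
- **That the overall test drops a selected group of patients.** The article says that "repeated measures, multivariate analysis of covariance (MANCOVA) will be used as an overall test for differences between groups" but states no rule for missing data. The remark that "many patients experience a first time episode of chest pain and, thus, do not feel limited in their daily activities" describes patients with little limitation. It does not report uncompleted forms. Intention to treat is defined there by allocated group, so no contradiction arises.

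**Conclusion.** The point holds in limited form and should be fixed.

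- **Improvement:** the stated baseline-to-follow-up comparison cannot be formed, and the ordinal test that reproduces the 81% is absent from the analysis text. That reproduction assumes 60 per arm, two-sided 5% and no dropout. The impossibility of the difference rests on no numerical assumption.
- **Worst pain:** the default is valid but generally less precise than ANCOVA, and the model choice is not fixed in advance. The variance excess is 11% to 67% for r from 0.8 down to 0.2 with equal SDs. At r = 0.5 it runs from none to about 133% as the SD ratio goes from 0.5 to 1.5. These figures illustrate the range; they do not predict this trial's loss.

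**What to change.** Replace the general sentences with one statement for each primary.

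- **Improvement:** compare the groups at follow-up with an ordinal test on all seven categories, either Wilcoxon rank-sum or proportional-odds regression, so that the analysis matches the sample-size basis. Keep the dichotomised number needed to treat as a secondary summary.
- **Worst pain:** analyse the follow-up score by ANCOVA with baseline worst pain as covariate, in all patients, regardless of any baseline comparison. Delete the conditional wording.

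The cost is wording only. Both ratings and baseline worst pain are already collected, and neither the sample size nor the visit schedule changes. The article describes the trial as ongoing, so the change should be recorded before outcomes are compared by arm.

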#### Cost-effectiveness analysis

A cost comparison of the therapy and advice group will be performed using data on direct and indirect costs. Cost differences between groups will be estimated using regression analysis where all chest pain-related costs in a year are regressed on treatment. A cost effectiveness analysis, using a mixed model linear regression analysis, will be conducted to compare the interventions, using patient-rated pain as the effective measure. Finally, a cost-utility analysis comparing the interventions will be performed using the EuroQol 5-D.

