### Health care cost/Cost-effectiveness analysis

Direct health care cost, direct non-health care cost and indirect cost are used in the economic evaluation as an indicator of cost-effectiveness. Cost data are collected through patient self-report questionnaires at 12 and 52 weeks. Direct costs for each patient will represent the one-year aggregated chest pain related health care costs based on utilization and estimated costs. Health care utilization (within and outside the study) is measured using standardized clinician treatment forms (each chiropractic visit, weeks 1–4), and patient rated self-report questionnaires (baseline and weeks 12 and 52). Direct health care costs include costs related to study treatment, non-study health care health provider use, medication utilization, and hospitalizations for chest pain. Indirect costs of productivity loss is measured by patient self-report (weeks 12 and 52) using questions that measure lost or impacted work or activity days due to chest pain. The EuroQol 5D (modified version) [35,36], a multi-attribute, patient self-report utility scale measuring five dimensions (mobility, self-care, usual activities, pain/discomfort, and anxiety/depression), is used as the cost-utility index. It is measured at baseline and weeks 4, 12, and 52.

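### The stated cost regression names treatment as its only regressor although health care use is collected at baseline; pre-specifying that covariate is a minor, nearly free gain in precision

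*Protocol article*

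**What the plan says.** The Cost-effectiveness analysis section of the protocol article describes three analyses.

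- Costs: "Cost differences between groups will be estimated using regression analysis where all chest pain-related costs in a year are regressed on treatment". Treatment is the only regressor named.
- Cost-effectiveness with patient-rated pain as the effect: "A cost effectiveness analysis, using a mixed model linear regression analysis, will be conducted to compare the interventions". No covariates are given.
- Cost-utility: "Finally, a cost-utility analysis comparing the interventions will be performed using the EuroQol 5-D". No model is given.

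The section headed Health care cost/Cost-effectiveness analysis describes the data. Utilization comes from clinician treatment forms and from "patient rated self-report questionnaires (baseline and weeks 12 and 52"). For the EuroQol 5D, "It is measured at baseline and weeks 4, 12, and 52". Cost data and productivity loss have no stated baseline measurement: "Cost data are collected through patient self-report questionnaires at 12 and 52 weeks", and "Indirect costs of productivity loss is measured by patient self-report (weeks 12 and 52").

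The article mentions baseline adjustment once, in the Randomized controlled trial part of Data analyses. There, ANCOVA for baseline variables is allowed where it is judged needed. The economic section does not repeat this.

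**The concern.** A regression of cost on a single binary treatment term is just the unadjusted difference in mean cost. Prior health care use is a natural candidate predictor of later health care use, and the trial already asks about it at baseline. Leaving it out has two consequences if it is prognostic: the cost difference is estimated less precisely than the collected data allow, and a chance difference in prior use between two arms of about 60 patients carries through into the estimated cost difference.

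Cost-effectiveness is among the stated aims. The sample of 120 was set on the improvement scale and not on costs, so precision that comes at almost no cost is worth having.

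**Working it through.** **Inputs from the article.** Intended RCT size is 120 (Randomized controlled trial section). Allocation is 1:1 (Randomization section), so 120/2 = 60 per arm. The only power figure, 81%, is for a shift on the improvement scale. With 60 per arm and an assumed two-sided 5% level it reproduces: 80.0% from a tie-corrected Noether calculation and 82.3% from a simulated Wilcoxon test. It says nothing about costs, and no figure is stated for the economic analysis.

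**Assumed input.** The correlation ρ between baseline utilization and one-year cost is not in the article. The calculation below uses a range and takes the cost regression to be linear.

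**Step 1: precision.** Adding a baseline covariate with correlation ρ multiplies the variance of the treatment contrast by about 1 − ρ², so the standard error is multiplied by √(1 − ρ²). An unadjusted analysis of 120 patients is then worth an adjusted analysis of 120 × (1 − ρ²).

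| ρ (assumed) | 1 − ρ² | SE ratio | SE reduction | Equivalent adjusted N |
|---|---|---|---|---|
| 0.1 | 0.99 | 0.995 | 0.5% | 118.8 |
| 0.2 | 0.96 | 0.980 | 2.0% | 115.2 |
| 0.3 | 0.91 | 0.954 | 4.6% | 109.2 |
| 0.5 | 0.75 | 0.866 | 13.4% | 90.0 |

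**Step 2: chance imbalance.** The between-arm difference in a baseline variable has standard deviation √(1/60 + 1/60) = 0.183 baseline SD, so 95% of randomisations fall within ±1.96 × 0.183 = ±0.36 SD. An imbalance of 2 standard errors (0.365 SD) shifts the unadjusted cost difference by ρ × 0.365 outcome SD: 0.07 at ρ = 0.2, 0.11 at ρ = 0.3 and 0.18 at ρ = 0.5. Averaged over randomisations the shift is zero.

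**Step 3: does another passage already supply the adjustment?** The ANCOVA sentence follows sentences on comparing baseline scores and on differences between baseline and follow-up. Total cost has no baseline score of that kind, because cost data are collected at weeks 12 and 52 only. Even if the sentence were read as covering costs, its conditional wording would leave the adjustment to be decided after the baseline data are seen.

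**The case against.** The strongest reply is that the article is condensed. It does not say that treatment is the sole regressor or that the model is unadjusted, and covariate lists often sit in a fuller plan that is not shown. That is fair as a caution. But the sentence does name an outcome, a method and a regressor, so it is a stated method that can be improved and not pure silence.

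Secondly, family doctor visits, hospitalizations and prescribed drugs are listed as secondary outcomes, so the ANCOVA provision arguably covers parts of health care use. This stands for those counts. It does not extend to the total-cost regression.

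Thirdly, the gain may be small, and this objection carries the most weight. Eligible episodes last under seven days, and the Discussion says many patients have a first-time episode, so prior chest-pain-related use may be close to zero for many. Productivity loss has no baseline counterpart. Study-treatment cost, which is included, is set largely by allocation.

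Three stronger readings are tempting and are not supported.

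- A reader might infer that the cost-utility and pain-based analyses are also unadjusted. The article gives no model for the first and no covariates for the second, so neither can be called unadjusted.
- A reader might infer bias or an inflated error rate. If ρ were 0.5 and the baseline imbalance 2 standard errors, the test statistic would follow N(1, 0.75) under no effect, and the conditional two-sided false-positive rate would be about 13%. But imbalances that large arise in only about 5% of randomisations, and over all randomisations the estimate is unbiased and the test keeps its level.
- A reader might infer a loss of stated power. The article sets out to estimate cost-effectiveness and states no economic test or power, so any such loss would be hypothetical.

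**Conclusion.** The point holds in a limited form. The cost model as stated omits a baseline covariate that the trial collects, and nothing else in the article clearly brings it in. This is a matter of precision and of chance imbalance in a given randomisation, not of validity. Its size rests entirely on an assumed correlation: the reduction in standard error runs from negligible (0.5% to 2% at ρ of 0.1 to 0.2) through about 5% at 0.3 to about 13% at 0.5. The features of this population make the lower part of that range credible. Minor, on a secondary analysis, and worth doing because it costs almost nothing.

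**What to change.** In the Cost-effectiveness analysis section, state that one-year chest-pain-related costs are regressed on treatment and on baseline chest-pain-related health care utilization from the baseline questionnaire, excluding the index admission. State also that this covariate is fixed in advance and is kept whatever imbalance is observed.

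The cost is one sentence, one degree of freedom, and a rule for the few patients with a missing baseline value; mean imputation of the baseline covariate is enough. No new data, visits or patients are needed. If the correlation proves low, the gain is small and almost nothing is lost.

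For consistency only, the plan could also say whether baseline EuroQol 5D enters the cost-utility comparison and baseline pain the mixed model. This is a suggestion and does not correct anything the article states.

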## Discussion

This study is the result of a unique research collaboration between researchers with backgrounds in chiropractic, cardiology, nuclear medicine and biostatistics, and to our knowledge this is the first randomized clinical trial investigating the effect of manual treatment on chest pain of musculoskeletal origin.

The design of this study has been a challenging process since no standardized and validated outcome measures for chest pain of musculoskeletal origin exists. The study by Christensen et al. [27] formed the basis for the present study. However, methods and results from the Christensen study are not directly applicable in this study, mainly because of differences in the two populations in terms of pain duration and other characteristics. Patients with chronic chest pain often have repeated pain episodes of a relatively mild character, sometimes described as "discomfort" [21]. They may experience pain that is brought on in familiar situations and at an expected work load. This is in contrast to patients with acute chest pain, who often experience a very dramatic and intense pain episode, some for the first time, and the pain evokes considerable anxiety and fear of cardiac conditions. In order to adapt to the differences in populations, a pilot study comprising 36 patients was conducted to determine the population size, inclusion and exclusion criteria, questionnaires, logistics and the primary outcome measures in the RCT. Following this, the semi-structured interview and pain rating scales were adjusted.

